**Method/design:**

In this three-arm randomized controlled trial, we plan to recruit 214 Polish students diagnosed with an adjustment disorder. Participants who meet initial eligibility criteria will be randomly assigned to one of three 6-week conditions: (1) online cognitive behavioural therapy intervention based on an existing, empirically supported transdiagnostic protocol, the unified protocol; (2) online progressive muscle relaxation training as an active control group; or (3) waiting-list control group. Both interventions are asynchronous, interactive, and include minimal amount of therapist support. Assessments will consist of self-report questionnaires, daily diary measures, and neurocognitive tasks for evaluating cognitive functioning. These will be conducted at baseline, post-treatment, and 1-month follow-up. Daily diary measures will be taken during the first and last week of treatment (or waitlist period). Primary outcome measures will include adjustment disorder severity; secondary outcome measures will consist of other negative (psychopathology: depression, anxiety, and stress) and positive (life satisfaction) indexes of mental health as well as process measures (e.g. mindfulness, experiential avoidance, cognitive fusion).

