Since the prevalence of academic adjustment problems is so high among this group and only half of students in need receive psychological help [32], it is important to develop and examine the effectiveness of an alternative—an online, self-help form of psychological assistance for students with AjD. It is also important to investigate the mechanisms of its effectiveness. Within the present literature on protecting students’ mental health, online therapy has been presented as an effective and potentially scalable solution [33]. To our knowledge, there has only been one study to date; it was focused on an online psychological intervention aimed at students with academic adjustment difficulties. It was based on an online meditation app available for commercial use. The study results suggest that individuals who used the app more frequently experienced more significant improvements in academic adjustment. Unfortunately, the study was limited by low app usage [34].

Internet interventions contain classic psychotherapy principles adapted to an online form. They can be fully automated—without psychotherapist support (unguided)—or allow therapist support [35]. They have been implemented worldwide for 20 years, but this area is still in its infancy in Poland [36], where there is a lack of both adapted e-interventions and research on their effectiveness [36]. Global data show that such programs can effectively treat mental disorders and be used in prevention efforts among student populations [37, 38].

Several studies have been published assessing the effectiveness of online therapeutic interventions aimed at people with AjD. All were based on CBT principles. Their promising results show small to medium effect-size improvements in experimental groups [39–42]. Unfortunately, these studies struggled with high dropout rates (50–80%) during the intervention. The percentage of people not helped by the interventions was also significant [43]. These studies relied on self-reported questionnaire methodologies, where it was impossible to determine any changes obtained in participants’ daily lives (at work, at school, or in family life). We intend to employ a more robust methodology and assess outcomes important for life in a university environment—such as cognitive functioning and academic performance. We will also study daily diary entries to increase the validity of results and obtain a more nuanced understanding of treatment effects.

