### Sample size calculation

The sample size was determined in relation to the between-group effect size and calculated using G*Power software. Previous research on an online UP intervention and online interventions for AjD has revealed a between-group effect size at the level of *d* = 0.5 and a within-group effect size at the level of *d* = 0.63 [42, 87]. Assuming an alpha 0.05 with a power of 0.80 and post-treatment between-group effect size of *d* = 0.5 (iCBT-UP versus control), 190 participants in the three groups will be sufficient to detect assumed differences. However, because the literature reveals dropout rates from online CBT interventions, with minimal guidance, of approximately 30% [88], a total sample of 247 participants will be recruited.

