### Trial status

This is the first version of the protocol, dated 2 February 2023. Recruitment will commence on 1 November 2023, with an estimated completion date of 1 March 2024. If we do not gather enough participants, we will continue the ongoing recruitment until we reach the estimated group sample size.

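### The recruitment target is 214 in the abstract and 247 in the sample size section, and neither leaves the stated 190 after the plan's own 30% dropout, because 247 is 190 × 1.30 rather than 190/0.70

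*Protocol article*

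**What the plan says.** Three places in the protocol article bear on the recruitment total.

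- **Abstract, Method/design:** "we plan to recruit 214 Polish students diagnosed with an adjustment disorder".
- **Sample size calculation:** the inputs are "Assuming an alpha 0.05 with a power of 0.80" and a between-group effect of d = 0.5 for iCBT-UP against control. The result is that "190 participants in the three groups will be sufficient to detect assumed differences". The section then cites "dropout rates from online CBT interventions, with minimal guidance, of approximately 30" per cent and, for that reason, says that "a total sample of 247 participants will be recruited".
- **Trial status:** if numbers fall short by the planned end date, "we will continue the ongoing recruitment until we reach the estimated group sample size". No total is given there.

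The Randomization and blinding section sets a 2:2:1 ratio for iCBT-UP, iPMR and the waiting list (WLC). The Data analysis section plans an intention-to-treat analysis of everyone randomized, with multiple imputation where appropriate. Trial status describes the document as the first version of the protocol, so neither total can be read as left over from an amendment.

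**The concern.** There are two linked faults.

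The first is a plain contradiction. The totals 214 and 247 differ by 33 participants, both are current text, and only 247 comes with a derivation. Because the recruitment-stop sentence refers to an estimated size without a number, a reader cannot tell from it when recruitment is complete.

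The second is the dropout step. To keep n people after losing a proportion p, one recruits n/(1 − p). The plan appears to have used n × (1 + p), which always falls short. The section presents 247 as the number that protects 190 against 30% loss, and it does not do so.

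At stake are the accuracy of the headline sample size and of the power claim attached to it.

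**Working it through.** **Inputs from the protocol article.** Required number 190, dropout 0.30, d = 0.5, alpha 0.05 and power 0.80 (Sample size calculation); totals 247 (same section) and 214 (Abstract); allocation 2:2:1 (Randomization and blinding).

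**Assumptions added here.** The test is a two-sided, two-sample t-test without baseline adjustment. Loss is equal across arms. Dropout means no observed post-treatment outcome.

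**1. Reproducing 190.** With equal arms and the normal approximation, n per arm = 2 × (1.960 + 0.842)²/0.5² = 62.8, so 63, and 3 × 63 = 189. The exact t calculation gives 64 per arm, and 3 × 64 = 192. The plan's 190 lies between these.

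**2. Reproducing 247.** 190 × 1.30 = 247.0, an exact match. The correct inflation is 190/(1 − 0.30) = 271.4, so 272. Check: 272 × 0.70 = 190.4.

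**3. What each total leaves at 30% loss.**
- 247 × 0.70 = 172.9, about 173.
- 214 × 0.70 = 149.8, about 150.

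**4. Loss each total can absorb while keeping 190.**
- 1 − 190/247 = 23.1%.
- 1 − 190/214 = 11.2%.

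**5. Power at d = 0.5, two-sided 0.05 (noncentral t).** Under 2:2:1 the arms are 40%, 40% and 20% of the observed total. Fractional arm sizes are used for 172.9 and 149.8.

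| Observed total | Arms at 2:2:1 | vs WLC | vs iPMR | Equal arms |
|---|---|---|---|---|
| 190 (the requirement) | 76 : 76 : 38 | 0.704 | 0.865 | 0.797 |
| 172.9 (from 247) | 69 : 69 : 35 | 0.662 | 0.831 | 0.758 |
| 149.8 (from 214) | 60 : 60 : 30 | 0.599 | 0.775 | 0.696 |

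The cost of the inflation error is the difference between the first two rows: 0.704 − 0.662 = 0.042 against WLC, 0.865 − 0.831 = 0.034 against iPMR, and 0.797 − 0.758 = 0.039 with equal arms.

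**6. What 272 would and would not repair.** It returns the trial to the first row, where two-sided power against WLC under 2:2:1 is 0.704. Reaching 0.80 for that contrast takes about 240 observed (96 against 48, power 0.802). That gap comes from the allocation ratio, not from the dropout step.

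**The case against.** **Everyone randomized is analysed.** Under the planned intention-to-treat analysis with multiple imputation, 173 is not the number analysed. This is right as to wording: 173 and 150 count people with observed post-treatment data. It does not rescue 247, because imputation does not recover all the lost information, and the sample size section itself chose to inflate for dropout.

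**The 30% may apply only to the two active arms.** These hold 80% of participants. Then 247 leaves 247 × (0.8 × 0.7 + 0.2) = 187.7 and 214 leaves 162.6. For 247 the gap nearly closes, but both remain below 190.

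**The stop rule most naturally means 247**, since that is the total the sample size section derives. This is a fair reading, but the text does not say so, and the abstract contradicts it. A reader might go further and infer that the ambiguity invites biased stopping in a trial with unblinded staff. The document describes no interim look at outcomes, so it does not support that inference.

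**Other stronger readings that the document does not support:**
- A reader might take the whole gap between 0.80 and 0.66 against WLC as the price of the arithmetic. Most of it is already there at 190, where power is 0.70.
- A reader might infer that 190 rests on a one-sided test, because a one-sided 76 against 38 comparison gives power 0.804 and 5 × 38 = 190. The section does not state sidedness, and equal arms with a two-sided test give 189 to 192, so the origin stays unknown.
- A reader might argue that 30% is contradicted by the Introduction, where "these studies struggled with high dropout rates (50–80%) during the intervention". That figure concerns leaving the intervention in earlier trials, which is not the same as a missing questionnaire. The 30% is cited for minimally guided online CBT, the support level planned here. Choosing between the two rates is a planning judgement, not an error.

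**Conclusion.** The point stands in two parts. The totals 214 and 247 conflict with nothing to reconcile them, and the recruitment-stop sentence does not say which applies. Separately, 247 is under-inflated: on the plan's own 190 and 30%, the total should be 272, and 247 protects 190 only up to about 23% loss (214 only up to about 11%).

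The contradiction and the arithmetic need no assumption beyond the document's figures. The effect on power is modest, about 3 to 4 percentage points for 247, and it rests on the t-test, two-sided alpha and equal loss assumed above. It is larger if 214 is the real target: against the 190 row, 0.704 − 0.599 = 0.105 versus WLC and 0.865 − 0.775 = 0.090 versus iPMR. A model using baseline scores could have higher power than shown, but that would not alter the counts.

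**What to change.** State one recruitment total and use it in the abstract, the sample size section and the recruitment-stop sentence in Trial status.

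The least costly course is to keep 247. The sample size section should then say that 247 leaves about 173 participants with observed outcomes at 30% loss, state whether the test is one- or two-sided, and give the power for each comparison under 2:2:1. On a two-sided basis this is about 0.66 against WLC and 0.83 against iPMR. This is corrected text in three places and no extra participants; the price is a less favourable stated power.

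If the sponsor prefers to quote 272 as the number that leaves 190, that is 272 − 247 = 25 more participants. The text should add that this corrects only the dropout step and does not give 80% two-sided power against WLC under 2:2:1.

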### Data analysis

All data will be analysed using the Statistical Package for the Social Sciences (SPSS) version v21.0 (IBM Corporation, Armonk, NY, USA). All randomized participants will be analysed, including those who stop receiving treatment on an intention-to-treat (ITT). The multiple imputation method will be used for missing data when appropriate. We also plan to perform sensitivity analysis to test the robustness against departures from the assumption of missing data being at random following the technique explained in Crameri et al. [89]. Hierarchical linear modelling will be used to assess our primary and secondary outcomes, daily diary results, and cognitive functioning. The most detailed level of analysis will contain results from daily diary measurements. The next level will be based on differences between each measurement. The last level in the model will include differences between each of the three groups. Hayes’ Process Macro will be used to assess mediation effects [90]. In this approach, effects are assessed using bias-corrected bootstrap confidence intervals. These effects are considered significant if the upper and lower bounds of the bias-corrected 95% confidence intervals do not contain zero. Mediation is assessed through the indirect effect of the independent variable on the dependent variable, mediated by an intermediate variable. For each statistically significant result, effect size will be calculated. The number of times each participant uses the program will be used to measure adherence. The results of this study will be submitted for publication in a peer-reviewed journal.

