### Objectives

The main objective of the planned research is to evaluate the effectiveness of an online UP intervention among students experiencing AjD.

More specific objectives are as follows: (1) evaluate the effectiveness of the intervention relative to waiting-list and active control groups according to self-reported measures; (2) investigate the effectiveness of the intervention in the daily lives of participants; (3) assess the effectiveness of the intervention in the cognitive functioning of students; (4) conduct an examination of predictors and mediators of treatment response; (5) compare the impact of both treatment approaches, with different putative mechanisms of action, on outcome measures; and finally (6) evaluate the maintenance of AjD alleviation at 1-month follow-up.

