### Randomization and blinding

Subjects who meet the inclusion criteria will be randomized to one of two active groups or the waiting-list group using a 2:2:1 allocation ratio. The participants will be randomly allocated using a computerized block randomization, using block sizes of 6. Random allocation will be performed using an algorithm developed by a computer scientist and executed independently of the research team by an independent program [49]. The main researcher will then reveal the concealed allocation and inform participants of their placement into one of three groups. Randomization will be stratified based on the score of the initial AjD questionnaire assessment (the IADQ; see description below). The principal investigator responsible for determining study eligibility will be blinded to the randomization sequence. The researchers and psychotherapists leading the study and contacting participants cannot be blinded to allocation for practical reasons; however, those conducting the MINI evaluation will be blind to the condition allocation during the assessment.

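### Effect sizes are tied to statistical significance, so the standardised effects reported would be a selected, upward-biased subset and a null iCBT-UP versus iPMR contrast would have none

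*Protocol article*

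**What the plan says.** The Data analysis section sets one rule on effect sizes: "For each statistically significant result, effect size will be calculated". It comes near the end of the section, after the model for the outcomes ("Hierarchical linear modelling will be used to assess our primary and secondary outcomes, daily diary results, and cognitive functioning") and after the mediation analysis.

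Confidence intervals are mentioned only for the mediation effects, where they act as a significance test: "These effects are considered significant if the upper and lower bounds of the bias-corrected 95% confidence intervals do not contain zero". The Primary outcome measures section plans to compare post-test IADQ scores and change from baseline across the three arms, and says nothing about effect sizes or intervals.

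Objective 5 is to "compare the impact of both treatment approaches, with different putative mechanisms of action, on outcome measures". Table 3 lists 12 questionnaire outcomes (IADQ, PHQ-9, GAD-7, SWLS, AAS, PSS-10, FFMQ-15, AAQ-II, SCS-SF, CFQ, PTQ, WEMWBS), plus daily diaries and the Stroop task.

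**The concern.** An estimate that is standardised and reported only after it has passed a significance test is, on average, too large, because the smaller estimates from the same true effect have been filtered out. With this many outcomes and three arms, a reader who sees the reported effect sizes sees the upper part of the distribution.

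The cost is highest for iCBT-UP versus iPMR. The article presents iPMR as an active and well-researched comparator, so a non-significant difference is a realistic result. The useful question is then whether the programmes perform alike or the trial is too imprecise to tell. A standardised effect with its interval answers that; under the rule as written it would not be calculated. Later syntheses also need the standardised effect whatever the p-value, and this trial's own sample size rests on effect sizes published by others.

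**Working it through.** The plan gives no figure for the consequence of this rule, so there is none to reproduce. The calculation below shows its size.

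**Inputs from the protocol article**
- Sample size calculation: "Assuming an alpha 0.05 with a power of 0.80 and post-treatment between-group effect size of" d = 0.5, and "190 participants in the three groups will be sufficient to detect assumed differences". (For d = 0.5 in equal arms, 63 per arm by the normal approximation or 64 by the t-test gives 189 or 192, so 190 is taken as it stands.)
- Randomization and blinding: participants are "randomized to one of two active groups or the waiting-list group using a 2:2:1 allocation ratio". Then 190 × 2/5 = 76, 76, and 190 × 1/5 = 38.

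**Assumptions**
- Two-sided 5% test (the article does not state sidedness), SD 1, a simple post-test contrast without baseline adjustment, and normally distributed estimates.
- True d of 0.2 and 0.3 are illustrative. The protocol states only 0.5 as a between-group effect.

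**Formulas**
- SE = √(1/n₁ + 1/n₂). An effect size is calculated only if |estimate| > 1.96 × SE.
- With x = d/SE, the chance of significance in the true direction is Φ(x − 1.96). The mean estimate given such significance is d + SE × φ(1.96 − x)/Φ(x − 1.96). The opposite tail is included in the table; it is negligible at d = 0.5.

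**iCBT-UP versus iPMR (76/76)**
- SE = √(1/76 + 1/76) = 0.162; threshold 1.96 × 0.162 = 0.32.
- At d = 0.5: x = 3.08, Φ = 0.869, φ = 0.2125. Mean reported effect = 0.5 + 0.1622 × 0.2125/0.869 = 0.54; ratio 1.08.

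**iCBT-UP versus waiting list (76/38)**
- SE = √(1/76 + 1/38) = 0.199; threshold 0.39.
- At d = 0.5: x = 2.52, Φ = 0.711, φ = 0.3417. Mean reported effect = 0.5 + 0.1987 × 0.3417/0.711 = 0.60; ratio 1.19.

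| True d | Contrast | No effect size calculated | Mean reported \|d\| | Ratio to truth |
|---|---|---|---|---|
| 0.5 | vs iPMR | 13% | 0.54 | 1.08 |
| 0.5 | vs waiting list | 29% | 0.60 | 1.19 |
| 0.3 (assumed) | vs iPMR | 54% | 0.44 | 1.47 |
| 0.3 (assumed) | vs waiting list | 67% | 0.52 | 1.73 |
| 0.2 (assumed) | vs iPMR | 77% | 0.41 | 2.06 |
| 0.2 (assumed) | vs waiting list | 83% | 0.50 | 2.48 |

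If every contrast is reported, the mean estimate equals the true d in each row.

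**Sensitivity at d = 0.5** (ratio versus iPMR, versus waiting list)
- Baseline adjustment, SE multiplied by √(1 − r²): with an assumed correlation r = 0.5, 1.03 and 1.11; with r = 0.7, 1.01 and 1.04.
- The article also says "a total sample of 247 participants will be recruited". If all 247 contributed full information (about 99:99:49), 1.04 and 1.11. This is a favourable bound, since imputation does not restore the missing information.
- If 30% of 247 contributed nothing (173 left, 69:69:35), 1.10 and 1.22.

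**The case against.** The strongest case against has four parts.

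- **The text does not say *only*.** It says what is done for significant results and forbids nothing for the rest. It also follows directly on the mediation sentences, so its scope could be disputed. This stands in part. But the sentence covers each significant result without limit, making the calculation conditional is its natural meaning, and no other section broadens it.
- **Estimates will exist anyway.** A reader might infer that null contrasts would have no estimate at all and be uninterpretable. The document does not support that. The hierarchical model gives a coefficient and standard error for each fitted contrast whatever its p-value, and an interval can be derived from them. If these were tabulated in full, the selection would affect only the standardised column. The article also offers anonymised data on request. This stands, and limits the point to standardised effects and to the absence of any commitment to report the rest.
- **The inflation is modest at the planned effect.** This also stands: it is 8% and 19% before baseline adjustment and less after it. A reader might take the two-fold figures as the expected bias; they depend on true effects that the protocol does not state.
- **Table layouts belong in an analysis plan.** True of the layout. But the article does more than leave effect sizes open: it fixes a conditional rule, and an analysis plan that followed it would carry the rule over.

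**Conclusion.** The point holds as a reporting flaw. The article makes effect sizes conditional on significance and makes no offsetting commitment for non-significant between-group contrasts. On the stated assumptions and the planned 190 analysed at 2:2:1, the mean reported effect at d = 0.5 is too large by a factor of about 1.08 (versus iPMR) and 1.19 (versus waiting list), and by less with baseline adjustment. At an assumed true d of 0.2 to 0.3 the factor is about 1.5 to 2.5.

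The practical loss is clearest for objective 5, where a null result would come without a standardised effect. The primary test, its type I error and the sample size are not affected. The sentence should be changed, but it does not threaten the trial's validity.

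**What to change.** Replace the sentence in the Data analysis section with:

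> The estimated between-group difference and standardised effect size, with 95% confidence interval, will be reported for every planned primary and secondary contrast regardless of statistical significance.

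The cost is one sentence and a little extra tabulation from models that will be fitted anyway. No new data, tests or participants are needed.

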### Governance and oversight of the trial

We will establish a trial management group (TMG) that will oversee the whole process of the research—recruitment of participants, assessments, ethical issues, adverse events, and data management. This group will meet once a week during the active phase of the research and in every case as the need arises. The group will consist of the principal investigator, the supervisor and co-principal investigator, and the trial platform manager. Due to the latest recommendations, adverse events will be investigated twofold. First is using our questionnaire outcome measures—to determine the number of patients who deteriorated and those who did not respond to the treatment. Second is using a self-report measure to detect adverse events administered post-treatment (described above) [85]. In case of any changes to the protocol, the TMG will communicate them to the investigators and participants and record them in the study diary.

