## Methods/design

### Study design

This study is a parallel group randomized controlled trial (RCT). The participants will be allocated to one of three 6-week conditions: (1) online cognitive behavioural therapy, based on the unified protocol (iCBT-UP); (2) online progressive muscle relaxation training (iPMR, active control group); and (3) waiting-list control group (WLC). The last group will receive access to their chosen intervention after the waiting period (6 weeks). To help WLC participants maintain motivation, weekly emails will be sent to remind them of the study and to assess their mood. They will be instructed to contact the research team in instances of any crisis. At that point, they will be administrated by our team psychotherapist or psychiatrist and referred to an adequate service. Assessments will consist of questionnaires, a cognitive task and a study of daily diaries. All assessments will be administered through an online data collection platform delivered by organisers (Supporty.pl), occurring at (1) screening, (2) baseline (prior to randomization), (3) at the end of the 6-week online program (or waitlist period), and (4) 1 month after finishing treatment (for participants in the active intervention conditions). Daily diary studies will be carried out for entries in the first and again in the last week of the interventions. Cognitive task will be administered at baseline, at the end of 6 weeks of online intervention, and 1 month after finishing treatment. The study will follow SPIRIT guidelines (Standard Protocol Items: Recommendations for Interventional Trials) [47].

Figure 1 shows the trial design. The study protocol and informed consent have been approved by the Ethics in Research Committee of the Faculty of Psychology, University of Warsaw.

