### Participant recruitment and inclusion and exclusion criteria

Participants will be recruited using announcements in popular social media and university newsletters. The study will be advertised to Polish students from different universities around the country. Interested participants will provide informed consent and then complete screening questionnaires. Those meeting preliminary eligibility criteria will then be assessed using the Mini-International Neuropsychiatric Interview (MINI) to ensure they meet Diagnostic and Statistical Manual of Mental Disorders, Fifth Edition (DSM-5) [48] diagnostic criteria for an AjD as a primary diagnosis and to establish comorbidities. The diagnostic interview will be administered by a trained psychologist or psychotherapist by video conference and then entered to the database.

The inclusion criteria consist of having student status, being 18 years old or older, having access to the internet and using a computer or smartphone, and meeting the diagnostic criteria of AjD in the IADQ questionnaire and meeting diagnostic criteria for AjD in the MINI.

The exclusion criteria consist primarily of conditions that require prioritization for immediate or simultaneous treatment: specifically, an increased risk of suicidality intent or ideation, bipolar and psychotic disorder, and/ or alcohol/substance use disorder. Individuals will also be excluded if they are receiving another psychological treatment at the start of the study or have no time to participate in the program. Pharmacological treatment during the intervention period will be allowed, provided that the type and dose of medication are stable for 6 weeks before study involvement.

Individuals not meeting the inclusion criteria will be referred to adequate services.

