### Risk management

Internet interventions used in the present study were not designed to provide crisis support for persons experiencing suicidal crises. We will exclude individuals with suicidal ideations and refer them to adequate services. We will also monitor participant mood using daily diary measures during the first and last week of the intervention and weekly throughout the intervention, by contacting participants through a chat function to assess any risk. In instances of crisis, we will organise a meeting with our team of psychotherapists and provide crisis support or refer the individual to an adequate service (psychotherapy, psychiatrist, or hospital).

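### Cheap improvement: efficacy is measured again at the one-month follow-up (t3), but no adverse-event question or risk contact is scheduled there, and the stated harms use of the questionnaires is only a count

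*Protocol article*

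**What the plan says.** Harms and risk are handled in four places in the protocol article.

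- **Entry.** The exclusion criteria cover "an increased risk of suicidality intent or ideation". The MINI diagnostic interview is marked in Table 3 at enrolment only.
- **During the intervention.** Under Risk management, mood is followed by diaries in the first and last week and "weekly throughout the intervention, by contacting participants through a chat function to assess any risk". The response is general: "In instances of crisis, we will organise a meeting with our team of psychotherapists", with support or referral to follow. No end date is given for this route.
- **Harms plan.** Governance and oversight describes two strands. In the first, the outcome questionnaires are used "to determine the number of patients who deteriorated and those who did not respond to the treatment". For the second it says: "Second is using a self-report measure to detect adverse events administered post-treatment". The Adverse events section words that question around negative effects in the treatment period, and Table 3 marks it at t2 alone.
- **Oversight.** The trial management group (TMG) has assessments, ethical issues and adverse events in its remit. On frequency: "This group will meet once a week during the active phase of the research and in every case as the need arises".

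Table 3 repeats the IADQ, PHQ-9, GAD-7, the other questionnaires and the cognitive task at both t2 and t3. Study design limits t3 to the active arms and says of data collection: "All assessments will be administered through an online data collection platform delivered by organisers".

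**The concern.** One of the protocol's specific objectives is to evaluate whether improvement is maintained at one month, so benefit is measured at t3. The harms schedule does not follow benefit to that point. The one adverse-event question has already been asked, its wording looks back only over treatment, and planned risk contact has ended with the intervention. The t3 forms are completed remotely, with no interview.

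The protocol itself treats risk as serious. It excludes suicidality at entry, cites an association between academic adjustment problems and suicidal ideation, and says the interventions were not built for suicidal crises. A participant in an active arm who worsens or is harmed after treatment would not be asked about it. If the t3 questionnaires showed the worsening, the only stated use is to add one to a count. This concerns participant safety and the completeness of harms reporting. It does not touch the primary endpoint, which is post-intervention IADQ.

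**Working it through.** No sample-size, power or alpha figure is at issue. The check compares the schedule with the text and does simple day arithmetic.

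**Inputs**
- Last intervention day: 42 (Table 3, second diary week).
- t2: 1 day after the intervention (Table 3).
- t3: 30 days after the intervention (Table 3), active arms only (Study design).
- Program access: 8 weeks (Interventions).
- Planned risk contact: weekly while the intervention runs (Risk management).
- Adverse-event question: t2 only (Table 3, Adverse events).

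**Dates, counting day 1 as the start of the intervention**
- t2 = 42 + 1 = day 43.
- End of program access = 8 × 7 = day 56.
- t3 = 42 + 30 = day 72.

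**Intervals before t3**
- From the nominal last risk contact: 72 − 42 = 30 days.
- From the only adverse-event question: 72 − 43 = 29 days.
- From the end of program access: 72 − 56 = 16 days.

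Day 42 is nominal. Participants may work at their own pace, so contact could be read as continuing until access ends on day 56. On that generous reading, 16 days before t3 still have no planned contact. At t2, by contrast, 56 − 43 = 13 days of access remain.

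**What is scheduled at each point**

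| | t2 (day 43) | t3 (day 72, active arms) |
|---|---|---|
| Efficacy questionnaires | yes | yes |
| Adverse-event question | yes | no |
| MINI interview | no | no |
| Planned weekly risk contact | ended the day before (nominal) | none |
| Program access | 13 days left | ended 16 days earlier |
| Stated harms use of questionnaires | count | count, if t3 data are included |

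The t2 question cannot cover days 44 to 72, because it is asked before them and refers to the treatment period. The deterioration count can draw on t3 data, but it is a group summary. Neither strand of the harms plan states that a t3 answer reaches the TMG or the crisis route as an individual case.

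**The case against.** The strongest case against has four parts.

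**Existing cover.** The TMG's remit includes assessments and adverse events. It meets weekly in the active phase of the research, which need not end when one participant's treatment ends, and also as need arises. Recruitment is staggered, so early participants may reach t3 while others are still in treatment. The crisis route has no end date. All of this stands. A reader might infer that the trial has no way to respond after treatment, and the document does not support that. What is missing is a scheduled step that brings a t3 answer to these bodies.

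**A coherent choice.** A question about the treatment period fits an assessment one day after treatment, and later worsening can appear in the deterioration count. This also stands, so the t2-only timing is not an internal contradiction. The count, however, does not ask about harms outside the scales and does not direct review of a person.

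**Suicidality on the PHQ-9.** A reader might infer that participants will report suicidal thoughts on the PHQ-9 at t2 or t3 and nobody will be told to look. The document does not support stating this as fact. It describes nine statements derived from DSM-IV depression criteria and never says that one concerns suicide. An item-level alert is also an operating detail that an article commonly leaves to the full protocol.

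**Timing.** Day 42 is not shown to be the last possible contact, and no section says when the chat closes. This is accepted; the 30-day interval is nominal.

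The condensed format does not answer the remaining point. The t2-only adverse-event row, the wording tied to treatment, and risk contact tied to the intervention are choices the article states.

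**Conclusion.** The point holds in a limited form. As written, nothing scheduled asks about harm arising between t2 (day 43) and t3 (day 72) in the active arms, and the only stated harms use of the t3 questionnaires is a count. The size is an interval of 29 days since the sole adverse-event question and nominally 30 days since planned risk contact, or 16 days if contact is assumed to last until program access ends. How many participants would be affected cannot be derived, and no number is claimed.

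The conclusion rests on Table 3 being the full assessment schedule and on the risk and governance sections describing the planned channels. It does not depend on what the PHQ-9 contains. It does not say that the trial lacks a crisis procedure or oversight, and it has no bearing on the primary endpoint or its analysis. It is a cheap safety improvement that should be made.

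**What to change.** 1. In Table 3 and the Adverse events section, repeat the adverse-event question at t3, worded to cover the period since treatment ended.
2. In Governance and oversight, state that t3 adverse-event answers, and marked individual worsening on the t3 questionnaires, go to the existing TMG and, if needed, to the crisis route under Risk management. The team should define marked worsening, and clinical action stays with the team.
3. State that this review takes place before identifiers are removed. The section on record retention and confidentiality plans irreversible removal, after which an answer could no longer be followed up.
4. Conditionally: if the PHQ-9 version used contains a suicidality statement (an assumption, since the document does not say so) and no alert procedure exists elsewhere, add a positive answer at t2 or t3 to the same routing.

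The cost is one more question at an online assessment that already takes place, so participant burden rises slightly. The TMG and crisis team take on some extra review work, including false positives, and someone must be available to respond while t3 data come in. No new instrument, visit or committee is needed.
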